**Figure 1 F1:**
[figure not shown]
**Sample Size**. N1: number of patients needed in the IPD group, P1: the chosen succes rate of the IPD group; P2: the succes rate of the decompression group (0.64); N2: number of patients needed in the decompression group (equal to N1); A: the alfa is two sided 0.05.

### Statistical analysis

Baseline comparability will be assessed by descriptive statistics to determine whether randomization was successful. Differences in outcome between both groups, together with 95% confidence intervals, will be calculated. Besides a difference in recovery between the two groups at two specified time points (eight weeks and one year), analysis of a difference in time to recovery will be carried out as well, using a survival analysis framework (COX hazards). All data are analyzed according to the "intention-to-treat-principle". Furthermore a repeated measurements analysis of variance will be performed on the underlying continuous scales. In all analyses the first assessment of treatment effect will be the estimate of the main effect within the appropriate model, adjusted for the stratification factors and main covariates. Secondly, an interaction term evaluating a possible effect modification of the treatment effect by the major covariates (see table 4: covariates for sub analysis) is pre-specified as being part of proper statistical modeling of the primary treatment effect. In the presence of severe interaction, the treatment effect will be presented as a function of the effect modifiers. In addition, an explorative subgroup analysis is conducted to investigate whether treatment effect varies over specific subgroups of patients (table 5: subgroups). Data will be stored via the internet-based secure data management system ProMISe of the department of Medical Statistics and Bioinformatics. The analyses will be carried out using appropriate statistical software (e.g. SPSS, version 17).

**Table 4 T4:** Covariates for subanalysis

N	Covariates for subanalysis
1	Age and age banding ( < 60 years, > 60 years or similar linked to groups size after recruitment)
2	Long medical history of back pain
3	Leg pain intensity
4	Proportion leg pain/back pain
5	Extent of stenosis during MRI examination
6	Kind of stenosis (soft or bony)
7	Sexe
8	Surface area of spinal canal

N, number of covariate (alphabetically ordered)

**Table 5 T5:** Subgroups

Subgroups	Variables
Demographics	age < 70 years versus > 70 years
	women versus men
Anamnestic and neurological variables	short versus long history of back pain
	more leg pain versus more back pain
Radiological variables	soft versus bony stenosis
	extent of stenosis during MRI examination

Subgroups bases on the following variables.

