## Methods/design

An observer and patient blinded randomized (cost-)effectiveness trial in the treatment of lumbar spinal stenosis is presented. In this trial two surgical techniques are compared in a parallel group design. The primary outcome measurement is the Zurich Claudication Questionnaire. The follow-up period will last 1 year. In order to collect enough patients, a multi-center design is necessary. The study protocol was approved in all participating hospitals (see table 1: list of hospitals).

**Table 1 T1:** list of hospitals participating in the Felix Trial

N	Hospital
1	Leiden University Medical Centre
2	Medical Centre Spaarne, Hoofddorp
3	Medical Centre Rijnland, Leiderdorp
4	Medical Centre Diaconessenhuis, Leiden
5	Medical Centre Haaglanden, The Hague
6	Medical Centre Bronovo, The Hague
7	Medical Centre Groene Hart, Gouda
8	Medical Centre Reinier de Graaf, Delft
9	Medical Centre Vlietland, Schiedam
10	Medical Centre Canisius Wilhelmina, Nijmegen
11	Medical Centre Haga, The Hague
12	Medical Centre Isala, Zwolle
13	Medical Centre Alkmaar
14	Medical Centre Tergooier, Hilversum
15	University Medical Centre Leiden

N, number of participating hospital in order of participating in this Felix Trial

Our primary question is whether IPD-surgery is more (cost-)effective compared with surgical decompression after 8 weeks in people with intermittent neurogenic claudication due to lumbar stenosis. The main advantage of IPD might be a faster recovery after surgery, but after long term follow-up it is unknown if this treatment effect will remain. Therefore, in addition, long-term follow-up (one year) will be compared with short-term follow-up.

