### Sample Size

The sample size calculation is based on the hypothesis that the short-term results obtained after IPD are equal to the results obtained after surgical decompression. The ZCQ at eight weeks will be used as a primary result measure both to answer the first research question and to calculate the sample size. The sample size of the trial is based on a superiority design and calculated under the alternative null-hypothesis to reach sufficient power to enable a distinction between the two arms in terms of success according to ZCQ if (according to the literature) results obtained after surgical decompression will be 64% and the results obtained after IPD will be at least 84% (20% difference in favor of IPD). A sample size of 98 patients per group ensures 90% power to confirm the null hypothesis when IPD is more than 20% superior to decompression, using a likelihood ratio test in a logistic regression framework (see figure 1: sample size). Accounting for about 10% loss to follow-up, this trial will enroll 216 patients with INC (108 patients in both groups). A sample size of 80 patients per group (including 10% loss to follow-up) will ensure a power of 80%. The feasibility of reaching 216 patients available for analysis will be checked after reaching 160 evaluable patients without deblinding or even analyzing the data as a group comparison. This constitutes a methodological valid approach since no multiple testing is involved and stopping further accrual is not based on an intermediate effect estimate. Since the power is based on a dichotomization of the underlying ZCQ scale, an alternative primary analysis of the ZCQ itself will also have sufficient power. The latter analysis will also take the repeated measurements structure into account.

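### The alternative primary analysis of continuous ZCQ is read from a repeated-measures main effect, with no 8-week contrast named, so its power claim is unsupported if the benefit is mainly short-term

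*Protocol article*

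**What the plan says.** The Methods/design section of the protocol article puts the primary question at 8 weeks and adds a one-year comparison because "after long term follow-up it is unknown if this treatment effect will remain". The Background hypothesises that the benefit of the interspinous device is chiefly short-term.

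The Sample Size section makes the 8-week ZCQ the primary result and sizes the trial on dichotomised ZCQ success. It then states that "an alternative primary analysis of the ZCQ itself will also have sufficient power", giving as its reason that the calculation was based on a dichotomised scale. It adds that this continuous analysis will account for the repeated measurements.

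The Statistical analysis section supplies the model, "Furthermore a repeated measurements analysis of variance will be performed on the underlying continuous scales", and the quantity to be read from it: "In all analyses the first assessment of treatment effect will be the estimate of the main effect within the appropriate model". The only interactions it names are those between treatment and the Table 4 covariates. It does not say which visits enter the model. Table 3 collects ZCQ at baseline and at 2, 4 and 8 weeks and 3, 6, 12, 24 and 60 months, so there are six follow-ups to 12 months and eight to 60 months.

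**The concern.** In a repeated-measures analysis of variance, the between-group main effect is the mean of the visit-specific group differences. It equals the 8-week difference only when the effect is the same at every visit or happens to average to the 8-week value. An analysis labelled primary would therefore estimate something other than the primary question.

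The power statement has the same gap. Avoiding dichotomisation is a good reason to expect more power from a continuous comparison at 8 weeks. It says nothing about a comparison averaged over later visits at which the effect may have gone. At stake is a second primary result that could be smaller than the 8-week effect, or non-significant, while a real 8-week benefit exists. The report would then hold two primary analyses that answer different questions.

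**Working it through.** **The plan's own figure.** Inputs from Sample Size and Figure 1: 64% against 84% success, 90% power, "A: the alfa is two sided 0.05".

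- The pooled two-proportion formula is n = [1.960·√(2·0.74·0.26) + 1.282·√(0.64·0.36 + 0.84·0.16)]² / 0.20² = 98.99, so 99 per group.
- Power at 98 per group is 89.7%, both by this formula and by the likelihood ratio test. The stated 98 per group reproduces, so the sample size for the dichotomised endpoint is not in question.

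**Assumptions for the continuous analysis.** The article gives no standard deviation or between-visit correlation for continuous ZCQ, so these are assumed.

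- The standardised effect at 8 weeks is taken from the plan's success rates on a latent normal scale: d = probit(0.84) − probit(0.64) = 0.994 − 0.358 = 0.636.
- The standard deviation is equal at each visit, and the correlation ρ is the same for every pair of visits, 0.5 or 0.7.
- There are 98 patients per arm, with follow-up visits only.

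**Formulas.** For k visits:

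- main effect = d × (mean of the visit effects relative to 8 weeks)
- variance of a patient's mean, in SD² units, v = [1 + (k − 1)ρ]/k
- SE = √(2v/98)
- power = Φ(effect/SE − 1.96)

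**8-week contrast.** SE = √(2/98) = 0.143 and 0.636/0.143 = 4.45, so power is 99%.

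**Main effect over six visits to 12 months.** For ρ = 0.5, v = 0.583 and SE = 0.109. For ρ = 0.7, v = 0.750 and SE = 0.124.

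| Pattern (2, 4, 8 wk, 3, 6, 12 mo) | Mean ratio | Main effect | Power, ρ = 0.5 | Power, ρ = 0.7 |
|---|---|---|---|---|
| 1, 1, 1, 0, 0, 0 | 0.50 | 0.318 | 83% | 73% |
| 1, 1, 1, 0.9, 0.6, 0 | 0.75 | 0.477 | 99% | 97% |
| constant | 1.00 | 0.636 | over 99% | over 99% |

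**Main effect over all eight visits to 60 months**, with no effect at 24 and 60 months in the first two patterns. For ρ = 0.5, v = 0.5625 and SE = 0.107. For ρ = 0.7, v = 0.7375 and SE = 0.123.

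- Effect to 8 weeks only: ratio 3/8 = 0.375, main effect 0.239, power 60% and 49%.
- Fading to zero by 12 months: ratio 4.5/8 = 0.5625, main effect 0.358, power 92% and 83%.

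**Sensitivity to the assumed effect.** Suppose instead that the 8-week effect is 0.463, which gives exactly 90% power for an 8-week contrast at 98 per arm, and let ρ run from 0.4 to 0.8.

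- Effect to 8 weeks only: 63% down to 43% over six visits, and 42% down to 27% over eight.
- Fading to zero by 12 months: 93% down to 76% over six visits, and 75% down to 52% over eight.
- Constant effect: 94% to over 99%, which is more than the 8-week contrast.

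**The case against.** The strongest reply is that the main-effect sentence is being read too literally. It governs all analyses, including the logistic and Cox models, where it cannot mean an average over visits. The next sentence sets it against covariate interactions. It may mean only that the treatment term comes before effect modification. That is plausible. But no other sentence says what is to be read from the repeated-measures model, so the ambiguity stands in an analysis called primary.

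Second, the 8-week question is answered elsewhere. The trial is sized on dichotomised success at 8 weeks ("A sample size of 98 patients per group ensures 90% power"), and a difference in recovery at 8 weeks and one year is planned separately. This stands: the trial does not lose its 8-week estimate, and the point is limited to the continuous analysis.

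Third, a reader might infer that the average halves the effect under the trial's own hypothesis. The documents do not support that. Halving needs the full effect at 8 weeks and none from 3 months, over six visits. The protocol calls persistence unknown, and its hypothesis gives no timing for any fading. With gradual fading over six visits at d = 0.64, little power is lost, and with a constant effect averaging gains power.

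Three further inferences should not be drawn.

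- Some repeated-measures software drops patients with a missed visit, but the article does not say that such patients are excluded. A mixed-model implementation would keep them, and missing-data handling may sit in the full protocol or SAP.
- For the same reason no breach of intention-to-treat is shown. The section says "All data are analyzed according to the" intention-to-treat principle, and nothing in the named model contradicts that.
- Sphericity concerns the within-patient tests of time and treatment-by-time. It does not bear on the between-group main effect, which is a comparison of patients' means.

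**Conclusion.** The point holds in a limited form. As written, the alternative primary analysis estimates an average over unstated visits and does not target the 8-week question. This mismatch does not depend on the pattern of the effect. The power loss does. At d = 0.64, ρ 0.5 to 0.7, 98 per arm and six visits, power against the 99% of an 8-week contrast is 73 to 83% if the effect ends after 8 weeks, about 97 to 99% if it fades to zero by 12 months, and undiminished if it is constant. Entering the 24- and 60-month visits, or a smaller true effect, makes the loss larger. The standard deviation structure, correlations, latent-scale effect and fading patterns are all assumptions. The statement of sufficient power is therefore unsupported under a mainly short-term benefit, though it is not shown to be false in general. The sample size for the dichotomised 8-week endpoint is unaffected.

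**What to change.** Replace the repeated-measures analysis of variance for continuous ZCQ by a linear mixed model on the available follow-up scores, with treatment, visit, treatment-by-visit and baseline ZCQ as a covariate. State which visits are included. Name the 8-week treatment contrast as the estimate for the alternative primary analysis and the 1-year contrast as secondary. Reword the power sentence so that it refers to the 8-week contrast.

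The change needs no new data or visits, only revised wording and a standard procedure. Its one statistical cost is that, if the effect is in fact constant, the 8-week contrast is somewhat less powerful than the visit average. At d = 0.463, that is 90% against 94% or more.

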## Discussion

In this article a design of a RCT is presented which evaluates the (cost-) effectiveness of IPD versus decompression surgery in the treatment of intermittent neurogenic claudication. This is the first randomized prospective trial comparing these two surgical techniques. Like the Sciatica-MED trial, the research nurse and the patient are blinded for the allocated treatment [7]. The objective of this trial is to determine whether the IPD is more (cost-) effective after eight weeks compared to the conventional decompression surgery.

## Abbreviations

CRF: case record form; INC: intermittent neurogenic claudication; IPD: interspinous process device; MCID: minimal clinically important difference; MRDQ: modified Roland disability questionnaire; MRI: magnetic resonance imaging; QALY: Quality adjusted live years; RCT: Randomized Controlled Trial; SF-36: short form-36; SWT: Shuttle walking test; VAS: visual analogue scale; ZCQ: Zurich claudication questionnaire.
